## 5.5 - Pre-operative safety

All patients enrolled in the trial will have been discussed at the weekly neuro-oncology tumor boards and deemed appropriate for the study based on eligibility and exclusion criteria (see section 4). All enrolled patients must sign the surgical consent and study consent.

5.6 - Surgery:

Patients will undergo surgery, which includes tumor resection and catheter placement, in the operating room. On the day of tumor resection, up to 4 barium-impregnated catheters (Medtronic Becker EDMS Ventricular Catheter 20cm Barium Impregnated cerebrospinal fluid ventricular catheters; Medtronic, Inc., Minneapolis, MN or equivalent) will be placed stereotactically into gadolinium-enhancing areas and/or in areas of FLAIR/T2 abnormalities. Prior use of ventricular catheters for intracerebral convection enhanced delivery has been approved by the U.S. Food and Drug Administration (BB-IND-9184) and published in peer-reviewed literature[[31](#_ENREF_31)]. Catheters can be placed stereotactically into infiltrated tumor areas unlikely to be resected or catheters can be advanced from the tumor cavity into surrounding brain. If there is no histologic confirmation of a malignant glioma via frozen section during tumor resection, for example in a case where the recurrent lesion actually represents another histologic entity such as radiation necrosis, catheters will not be placed.

The surgical procedure which is conducted in an operating room at OSU Main Hospital will include standard craniotomy steps such as skin incision, removal of part of the skull, opening the dura, identifying and resection the recurrent brain tumor and achieving hemostasis. At this point during standard tumor resection, the tissues would then be closed and the surgery would conclude. This would include closing the dura, affixing the bone flap to the skull with titanium plates and suturing the overlying soft tissues back together. Instead, prior to closing the dura, two to four infusion catheters will be placed into the brain surrounding the resection cavity. Each catheter will then be tunneled under the scalp and through the skin such that the end of the catheter is outside of the head and accessible after surgery. A luer lock cap will be secured to the catheter such that it can subsequently be connected to the infusion system. The dura is sutured together and bone flap reaffixed to the skull in the standard manner, with the only difference being that the catheters traverse these tissues. The catheters pass throught the skin at a different site than the skin incision. This procedure by which catheters are brought from the intracranial cavity to outside of the head is identical to that used for placement of a variety of cranial catheters such as intraoperative placement of ventriculostomy catheters and subdural drains, both of which are common neurosurgical procedures.

5.7 - Carboplatin infusion:

Patients enrolled in the study will undergo craniotomy for tumor resection. During this surgery, at the conclusion of tumor resection, they will have stereotactic insertion of up to 4 catheters into the area surrounding the resection cavity. Catheter placement will be performed by the neurosurgeon performing tumor resection. Catheter placement will occur during the same surgery as the tumor resection; a second surgery for catheter placement is not required. Carboplatin infusion will commence after postoperative CT confirmation of catheter placement. . Carboplatin infusion will not occur in the operating room. Infusion will proceed for 72 hours at which point the catheters will be removed at the bedside. The patient will be monitored in the hospital for an additional 12-24 hours prior to discharge.

5.8 - Assessments:

CT within the first 12 hours after surgery will verify catheter placement. MRI will be performed after catheter removal to assess, if possible, the volume of distribution of the infusate. While the patient is in the hospital, clinical evaluation will be performed per standard neurological-critical care guidelines. Carboplatin infusion and patient monitoring during the hospitalization will be conducted by the patient’s medical team including the neurosurgeon who performed the procedure, neuro-oncologist, nursing team and associated house staff. Thereafter, study patients will be evaluated clinically every 4 weeks for the first 16 weeks and every 8 weeks until 30 weeks. Evaluation will include full neurological and general examination, mini-mental status examination, and Karnofsky Performance Status. Serum carboplatin levels will not be assessed. MRI, performed every 2 months, will be evaluated per McDonald criteria. Additional ancillary imaging will be used when imaging changes are suggestive of a treatment related effect, or if the clinical scenario requires. Toxicity will be assessed according to the National Cancer Institute Common Terminology Criteria for Adverse Events, Version 4.0.

5.9 - Postoperative care and carboplatin infusion:

Immediate postoperative management will occur in the hospital and will follow the routine standard of the neurosurgeon and the neuro-oncology team. Vital signs and neurologic status will be assessed by nursing as per standard ICU protocol and recorded hourly for the first 24 hours after surgery and then at least every 8 hours for the remainder of hospitalization. Daily labs as per the study calendar will be assessed (see section 7). Infusion of carboplatin will occur in the hospital, primarily in the James Hospital, and will be initiated after CT confirmation of catheter location.

A CT will be obtained a maximum of 12 hours before the start of the infusion to confirm catheter position. Infusions will start preferably on postoperative day 1, but could be delayed up to postoperative day 7, based on patient’s condition. If the patient’s condition does not allow for infusion, the catheters will be removed. Once catheter placement has been confirmed, patients will undergo infusion of carboplatin. Carboplatin will be infused at a rate of 0.75 mL per hour over 72 hours via a syringe pump. The total flow rate (0.75 ml/hr will be divided among the catheters placed. The catheters and syringe pumps will be attached to a bedside programmable syringe-type microinfusion pump (Medex/Medfusion 3500 Syringe pump or equivalent, which are immediately available for use) via infusion tubing (Vygon Neuro Infusor Infusion catheter system).

The infusion pump will be monitored by the surgical team, including attending neurosurgeons, resident house staff and nurse practitioners. Decisions regarding initiation of infusion and determining if there are problems with the infusion will be the responsibility of the surgical team and supervised by one of the neurosurgical attending physicians ([name]). The infusate will be prepared and supplied by The OSUMC / James Pharmacy Investigational Drug Service (see section 3) at the dose as determined by the dosing schedule (see page 18, section entitled ‘dosing paradigm’) and will be changed every 24 hours by the surgical team. A syringe-type microinfusion pump (see paragraph above) will control the rate of carboplatin infusion into the infusion catheter. The syringe will connect to the infusion catheters via infusion tubing. The infusion rate will be 0.75 ml/hr. Nursing staff will record that the infusion is running, but will otherwise have no responsibilities regarding the infusion pump. For any problems with the infusion or if the infusion pump alarms, the nurses will notify the neurosurgical team. During infusion, vital signs and neurologic status will be assessed and recorded at least every 4 hours. A specific person designated for monitoring the infusion pump and this person’s contact information will be clearly identified in the chart and provided to the patient’s nurse. This person will be a member of the neurosurgical team and will be [name], [name] or [name] or a physician or nurse directly supervised by [name], [name] or [name].

## 5.10 - Inpatient care

All patients will be admitted to the neurosurgical intensive care unit (NICU) after surgery. They will receive standard postoperative care including hourly vital sign and neurologic assessment. Patients will be transferred from the NICU to the stepdown unit or ward based on their clinical status. They will remain in a monitored setting (ICU, stepdown unit or ward) for the duration of their infusion, receiving continuous vital sign monitoring and frequent medical and neurologic examinations. Once the catheters have been removed, they will receive standard postoperative care provided to patients who have had craniotomy for brain tumor resection.

The admitting neurosurgeon and house staff will be responsible for documenting daily neurologic and medical examinations and responding to any acute changes in neurologic or medical status. A separate NICU attending and house staff team will provide additional examinations while the patient is in the NICU. Daily blood tests will monitor for marrow suppression, electrolyte imbalances and liver dysfunction.

CT within the first 12 hours after surgery will verify catheter placement and assess for intracranial hemorrhage. MRI will be performed after catheter removal to assess for residual enhancement and, if possible, the volume of distribution of the infusate. While the patient is in the hospital, clinical evaluation will be performed per standard neurological-critical care guidelines. Baseline examinations prior to surgery and 24 hours after surgery will include full neurological and general examinations, mini-mental status examination and Karnofsky Performance Status.

Neurologic status will be monitored as per standard of care for postoperative brain tumor resection patients and is described in sections 5 and 7. Daily examinations will be conducted by the surgeon ([name], [name]) and house staff (residents). Serial vital signs and neurologic assessments by nursing staff will occur as per standard of care, including hourly assessments in the ICU during the first 24 hours after surgery and assessments every 4-8 hours thereafter. This may be adjusted based on the clinical/neurologic status of the patient. Neurologic examinations include an assessment of mental status including level of arousal and orientation, cranial nerve examination and motor/sensory examination of the extremities. Of note, the toxicities in primate studies referenced in the protocol were in a protocol for carboplatin infusion into the brain stem. We will not be performing infusion into the brain stem or any other eloquent structure as per the protocol.

5.11 - Post-discharge care / Outpatient monitoring:

Post-operative outpatient visits, laboratory tests and imaging will be in the James clinic and OSU outpatient testing facilities and will adhere to the calendar provided in the section 7.

After discharge, study patients will be evaluated clinically every 4 weeks for the first 16 weeks and every 8 weeks thereafter until 30 weeks. Evaluation will include full neurological and general examination, mini-mental status examination, and Karnofsky Performance Status. MRI, performed every 8 weeks, will be evaluated per McDonald criteria by a neuroradiologist (see below). Additional ancillary imaging will be used when imaging changes are suggestive of a treatment related effect, or if the clinical scenario requires. Toxicity will be assessed according to the National Cancer Institute Common Terminology Criteria for Adverse Events, Version 4.0

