## 6.7 - Data Saftey Monitoring Plan

The data and safety monitoring plan will involve the continuous evaluation of safety, data quality and data timeliness. Investigators will conduct continuous review of data and patient safety at their regular Disease Group meetings (at least monthly) and the discussion will be documented in the minutes. The PI of the trial will review toxicities and responses of the trial where applicable at these disease center meetings and determine if the risk/benefit ratio of the trial changes. Frequency and severity of adverse events will be reviewed by the PI and compared to what is known about the agent/device from other sources; including published literature, scientific meetings and discussions with the sponsors, to determine if the trial should be terminated before completion. Serious adverse events and responses will also be reviewed by the OSUCCC Data and Safety Monitoring Committee (DSMC). The PI will also submit a quarterly progress that will be reviewed by the committee per the DSMC plan. All reportable Serious Adverse Events (SAE) will also be reported to the IRB of record as per the policies of the IRB.

|  | Within 4 weeks prior to catheter Placement | Day of surgery, catheter placement, and infusion | Day after surgery | Post-infusion day 1 | Day 7 | Day 14 | Day 28 | Week 8 | Week 12 | Week 16 | Week 22 | Week 30 |
| --- | --- | --- | --- | --- | --- | --- | --- | --- | --- | --- | --- | --- |
| Informed Consent | X |  |  |  |  |  |  |  |  |  |  |  |
| Inclusion/Exclusion  Criteria | X |  |  |  |  |  |  |  |  |  |  |  |
| Pathology | X | X |  |  |  |  |  |  |  |  |  |  |
| Medical History | X |  |  | X |  |  | X | X | X | X | X | X |
| Concomitant Meds | X | X |  | X |  |  | X | X | X | X | X | X |
| Physical Exam and Vital Signs | X | X | X | X |  | X | X | X | X | X | X | X |
| Neurological examination | X | X | X | X |  | X | X | X | X | X | X | X |
| MMSE | X | X | X | X |  | X | X | X | X | X | X | X |
| Performance Status Determination | X | X | X | X |  | X | X | X | X | X | X | X |
| CBC with differential and platelets, | X | X | X | X | X | X | X | X | X | X |  |  |
| Comprehensive Metabolic Profile | X | X | X | X | X | X | X | X | X | X |  |  |
| Pregnancy Testing | X |  |  |  |  |  |  |  |  |  |  |  |
| MRI Brain^1^ | X |  |  |  |  |  |  | X |  | X |  | X |
| AE monitoring | X | X | X | X | X | X | X | X | X | X | X | X |
| CT Brain |  | X |  |  |  |  |  |  |  |  |  |  |

7 – Study Calendar

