## 8.2 - Secondary endpoints

Secondary endpoints include evaluations of efficacy and drug distribution. Evaluations of efficacy will include assessing the six-month progression free survival and median progression free survival, as well as the radiographic response rate. Volume of distribution of infusate will be evaluated radiographically by post-infusion MRI. Six month progression free survival is defined as the proportion of patients with stable disease at 6 months from surgery. Progression free survival is defined as time between surgery and earliest sign of disease progression or death. Overall survival is defined as the time from surgery until death.

Radiographic and Clinical Response Criteria

8.2.1 - Neurological Examination Status (compared to baseline assessment)

| Better | Must be on stable or decreasing dosage of corticosteroids |
| --- | --- |
| Stable | Failure to qualify as better or worse |
| Worse | Includes patients requiring increasing steroid dosage to remain stable |

If a patient requires a higher dose of steroid to maintain a stable neurological status, the patient will be considered worse for the purpose of response determination.

Patients who are clinically worse but whose steroids have been decreased at the time of deterioration will be considered stable until reassessed again at the baseline steroid dosage.

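### The text calls for MRI every 8 weeks but the calendar has none between weeks 16 and 30, so no scheduled scan falls near six months and six-month PFS can be biased in either direction

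*Protocol*

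**What the plan says.** - Section 5.8 (Assessments): "MRI, performed every 2 months, will be evaluated per McDonald criteria".
- Section 5.11 (Post-discharge care / Outpatient monitoring): "MRI, performed every 8 weeks, will be evaluated per McDonald criteria by a neuroradiologist". The same section says that outpatient visits, laboratory tests and imaging "will adhere to the calendar provided in the section 7".
- Section 7 (Study Calendar): the last three columns are "Week 16 | Week 22 | Week 30". The MRI row is marked before surgery and at weeks 8, 16 and 30. Week 22 has physical and neurological examination, MMSE and performance status, but no MRI. A footnote adds an MRI after catheter removal.
- Section 8.2 (Secondary endpoints): "Six month progression free survival is defined as the proportion of patients with stable disease at 6 months from surgery". Also: "Progression free survival is defined as time between surgery and earliest sign of disease progression or death". Neither definition names the scan or window that settles status at six months.

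**The concern.** Section 5.11 contradicts itself. A site cannot scan every 8 weeks and also follow a calendar with a 14-week interval between MRIs. The interval contains the six-month time point, which is the landmark of the first-named efficacy measure in section 1.2.

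Stable disease in section 8.2.2 is a radiographic category, so status at six months needs an image. Under the calendar, a progression without symptoms that begins after week 16 has no scheduled means of detection until week 30. Whether that patient counts as progression-free at six months then depends on a convention and not on an observation. Section 1.2 says that the efficacy results are to support future trials, so a figure that depends on the scan calendar could be carried forward into their planning.

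**Working it through.** The protocol gives no expected six-month PFS rate, so there is no figure of its own to reproduce. The check asks how far the scan schedule alone can move the estimate.

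**Inputs**

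- Six months = 6 × 365.25/12/7 = 26.1 weeks. Distance to the calendar scans: 26.1 − 16 = 10.1 weeks and 30 − 26.1 = 3.9 weeks.
- Median PFS of about 3 months and median overall survival of about 9 months are the only such human figures in the protocol (section 2.3). They describe phase II studies of intravenous carboplatin and are not planning values for this trial. A range of 2 to 6 months for median PFS is therefore assumed.
- Exponential PFS is assumed: S(t) = 0.5^(t/median).

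**Step 1. Which scan settles six-month status**

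The estimate equals S(16) if progression is found only on scheduled MRI and week-16 status is carried forward. It equals S(24) with scans at weeks 8, 16 and 24, and S(30) if the week-30 scan is taken as the six-month result. The true value is S(26.1). For a 3-month median (13.04 weeks), S(16) = 0.5^(16/13.04) = 42.7%. Values are in per cent and differences in points, taken before rounding:

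| Median PFS (months) | S(16) | S(24) | S(26.1) | S(30) | Week 16 − true | Week 24 − true | Week 30 − true |
|---|---|---|---|---|---|---|---|
| 2 | 27.9 | 14.8 | 12.5 | 9.2 | +15.4 | +2.3 | −3.3 |
| 3 | 42.7 | 27.9 | 25.0 | 20.3 | +17.7 | +2.9 | −4.7 |
| 4 | 52.9 | 38.4 | 35.4 | 30.3 | +17.5 | +3.1 | −5.1 |
| 6 | 65.4 | 52.9 | 50.0 | 45.1 | +15.4 | +2.9 | −4.9 |

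The part of the upper-case excess that is due to the calendar, as against the 8-weekly text, is S(16) − S(24). This is 12.5 to 14.8 points over the same medians.

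**Step 2. Some progressions found clinically (3-month median)**

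Let f be the share of week 16 to 26 progressions found through symptoms before week 26. The bias is (1 − f) × 17.7 points:

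- f = 25%: +13.3
- f = 50%: +8.9
- f = 75%: +4.4

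If detection happens only at the week-22 visit, with S(22) = 31.1%, the bias is S(16) − f × [S(16) − S(22)] − S(26.1). This gives +14.8, +11.9 and +9.0 points for f = 25%, 50% and 75%.

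**Step 3. Deaths counted as events**

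A simulation with median PFS 3 months and median overall survival 9 months, in which progression is otherwise found only at scheduled scans, gives 39.7% under the calendar and 27.8% under scans at weeks 8, 16 and 24. The true value is 25.0%. The excess under the calendar is +14.7 points against the truth and +11.9 points against the 8-weekly schedule.

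**Step 4. Sampling error for comparison**

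With the maximum of 42 patients (section 9) and a rate of 25%, the 95% half-width is 1.96 × √(0.25 × 0.75/42) = 13.1 points.

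**The case against.** The strongest reply is that the protocol does not rely on scheduled MRI alone. PFS runs to the earliest sign of progression or to death. Week 22 has a full neurological assessment. Section 8.2.1 classes a patient who needs more steroid to stay stable as worse. Section 5.11 allows extra imaging when the clinical situation requires it, section 8.2.3 re-images unresolved cases in 4 weeks, and section 8.2.4 scans responders every 6 weeks. The deciding scan, visit windows and missing-scan rules are also commonly left to a statistical analysis plan, which is not at hand. Finally, six-month PFS is a secondary endpoint with descriptive analysis only, and no dose decision depends on it.

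Most of this stands, and it limits the size and the priority of the point. A reader might infer that six-month PFS is simply overstated by 15 to 18 points, or that it is really a four-month figure. The protocol does not support that. Those figures need detection on scheduled MRI only and week-16 status carried forward, and the protocol fixes neither. Deaths and clinically detected progressions up to week 26 still count. If the week-30 scan decides, the sign reverses.

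A reader might also infer that overall survival is cut off at week 30 because the calendar ends there. Nothing says so. The 30-week limit applies to clinical evaluations, and "Overall survival is defined as the time from surgery until death".

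Two things are not answered by the reply. Sections 5.8 and 5.11 and the calendar still disagree, and an analysis rule cannot recover a scan that was not taken. The clinical safeguards also need a trigger: a patient with stable disease and no symptoms has no scheduled image between weeks 16 and 30.

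**Conclusion.** The contradiction is established from the text alone. Its consequence is that six-month PFS can be biased by an amount and a sign that the protocol leaves open:

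- up to about +15 to +18 points if progression is found only on scheduled MRI and week-16 status is carried forward (median PFS 2 to 6 months);
- about +4 to +13 points at a 3-month median if 75% to 25% of progressions are found clinically;
- about −3 to −5 points if the week-30 scan decides.

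Scans at weeks 8, 16 and 24 would leave about +2 to +3 points. All of these rest on exponential PFS and on an assumed range of medians. The 3-month value is background for a different route of administration.

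This should be corrected, but it does not touch the primary objective of dose-limiting toxicity and MTD. Sampling error with at most 42 patients is of similar size to the larger biases. Unlike sampling error, however, a bias built into the schedule does not shrink with more patients.

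**What to change.** Reconcile sections 5.8 and 5.11 with the section 7 calendar so that one MRI schedule applies and a scheduled scan falls close to six months. Continuing the calendar's own weeks 8 and 16 at the 8-weekly interval in the text would put it at about week 24. The text does not name the origin of the interval, so the week should be written out. Adding the MRI to the existing week-22 visit would help less: at a 3-month median, S(22) − S(26.1) = 31.1% − 25.0%, about 6 points, against about 3 points for week 24.

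State in section 8.2, or in the analysis plan if one exists, that this scan decides six-month PFS and within what window. A patient whose progression is first seen at week 30, with no earlier scan in the window, should not be counted as progression-free at six months. An interval-censored estimate is an alternative.

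The cost is a correction to the calendar and one analysis rule. The extra scan is one that the 8-weekly text already implies. The downside is a possibly less favourable PFS figure. The change helps most if made before further patients pass week 16.
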